# Effects of electroacupuncture frequencies on chronic low back pain in older adults: triple-blind, 12-months protocol for a randomized controlled trial

**DOI:** 10.1186/s13063-019-3813-6

**Published:** 2019-12-23

**Keywords:** Acupuncture, Aged, Clinical trial, Electroacupuncture, Low back pain

## Abstract

**Background:**

Low back pain (LBP) is the most frequent complaint in clinical practice. Electroacupuncture treatment may be effective; however, the supporting evidence is still limited, especially in older adults.

**Objective:**

The current study is a randomized controlled trial that aims to evaluate the clinical efficacy of electroacupuncture in older adults with LBP.

**Methods:**

A five-arm randomized controlled trial with patients and evaluators blinded to the group allocation. A total of 125 participants with non-specific LBP will be randomly assigned into one of five groups: three electroacupuncture groups (low, high, and alternating frequency); one control group; and one placebo group. The electroacupuncture will be applied twice a week (30 min per session) for five weeks. The primary clinical outcome measure will be pain intensity. The secondary outcomes include: quality of pain; physical functioning; perceived overall effect; emotional functionality; patient satisfaction; and psychosocial factors. Patients will be evaluated before the first session, immediately after the last, and followed up after six and 12 months to check the medium- and long-term effects.

**Discussion:**

Although electroacupuncture is increasingly used to treat LBP, there is no guidance regarding the parameters used, which leads to inconsistent results. Thus, the effect of electroacupuncture (EA) on LBP remains controversial and requires more studies, especially in the older adult population.

**Conclusion:**

This is the first randomized controlled trial to evaluate the efficacy of different frequencies of electroacupuncture for treating chronic LBP in older adults. This study will provide evidence on the effectiveness of electroacupuncture as an alternative treatment method for LBP and will entail wider debate about an appropriate acupuncture intervention in this population.

**Trial registration:**

Clinicaltrials.gov, NCT03802045. Registered on 14 January 2019.

## Background

Low back pain (LBP) is the most frequent complaint in the clinical practice, with approximately 80% of the world population presenting with at least one episode throughout their lives [1]. Approximately six million older adults suffer from chronic LBP [2], with a prediction of increase in the coming years due to rapid and progressive population growth and aging [3]. These data are worrisome, since the elder population is the second most common age group to visit physicians due to LBP. This musculoskeletal condition is considered one of the main causes of disability worldwide, being strongly associated with functional incapacity, sleep disorders, withdrawal from social and recreational activities, psychological distress, cognitive deterioration, and falls in older adults [4, 5].

Pain is the main factor responsible for these harmful outcomes, therefore the treatment focuses mainly on analgesia and requires a combination of pharmacological and non-pharmacological therapies, where the latter should be emphasized [6]. Acupuncture is among the non-pharmacological strategies, the effects of which can be potentiated by electroacupuncture (EA). EA allows the stimulation of a larger area around the acupoint for a shorter time and, especially, allows parameters such as intensity, duration, and frequency of the stimulus to be easily identified and quantified [7].

However, the studies recommending EA as an effective and viable option for treating chronic LBP have methodological discrepancy regarding acupuncture techniques and procedures, with no guidelines regarding the standardization and efficiency of this treatment, which makes the healing effect of acupuncture controversial [8–10]. Hence, there is a need for rigorously studies that explore the acupuncture methods related with its therapeutic efficacy in order to improve validity of randomized clinical trials about acupuncture and EA in LBP [11].

Considering the prevalence of LBP in older people, the significance of health problems associated with this painful condition, and the lack of evidence in acupuncture guidelines, a thorough designed randomized controlled clinical trial is proposed.

### Study objectives

This study aims to evaluate the clinical efficacy of EA in older adults with LBP.

Our primary study goal is to screen a dominant EA frequency on pain management and its secondary outcomes in EA groups.

Our second goal is to determine whether EA is a more effective treatment than acupuncture (control) and placebo in older people with chronic LBP, in a one-year randomized controlled trial (RCT) (NCT03802045).

Our third goal is to determine the long-term effect of the EA, acupuncture, and placebo on LBP in older adults after six months and one year at the end of treatment.

### Trial design

This study is a five-arm clinical RCT with blinded patients and evaluators.

## Materials and methods

### Study setting

The study will be conducted at the University of São Paulo (USP) in partnership with the Federal University of Paraná (UFPR), both in Brazil. The study was approved by the Research Ethics Committee of the Medical School of USP (authorization no. 2.903.991) and financed with the authors’ own resources.

### Recruitment

Participants will be recruited through radio ads, social networks, and local newspapers. Individuals will be informed about the research proposal and treatment protocol, and those interested in participating will be selected according to the inclusion and exclusion criteria.

### Participant timeline

The participant timeline is shown in Fig. 1.

**Fig. 1 Fig1:**
[figure not shown]
Study timepoints

### Inclusion criteria

We will use the World Health Organization (WHO) cut-off point of ≥ 60 years to refer to the elderly population in resource-poor countries [9]. Patients of both genders will be included. Other criteria are: (1) medical diagnosis of non-specific LBP of > 3 months’ duration; (2) with or without radiating leg pain; (3) a minimum pain intensity score of 4 on the 11-point pain numerical rating scale (NRS; Brazilian Portuguese version); (4) walk independently (with or without walking devices); and (5) signing of the consent form.

### Exclusion criteria

Patients will be excluded if: (1) they have had previous surgery on the spinal column; (2) have a known or suspected serious spinal pathology (e.g. cancer, vertebral fracture, spinal infection, or cauda equina syndrome); (3) fear of needles; (4) have participated in acupuncture treatment in the previous 30 days; or (5) if they are wheelchair users.

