### Qualification of practitioners

The interventions will be performed by acupuncture specialists with at least three years of clinical experience, who will receive prior training to ensure that they rigorously follow the study protocol and are familiar with the types of treatments, including details such as acupuncture points and manipulation of electroacupuncture parameters.

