### Procedures

After randomization, the acupuncturist will sequentially open the envelopes and the individuals will be randomly assigned to one of five treatment groups, each containing 25 participants: low frequency EA (LF); high frequency EA (HF); alternating frequency EA (AF); control group (C); and placebo group (P). The acupuncture points will be located and described according to the WHO Standard Acupuncture Locations [24]. Based on the beneficial effects of previous clinical trials, the acupoints selected for this study will be: BL23, BL25, BL40, SP6, and KI3 [10, 25–27] (Table 1).

**Table 1 Tab1:** Protocol for acupoints

Acupoints	Location
BL23 (Shenshu)	In the lumbar region, at the same level as the inferior border of the spinous process of the second lumbar vertebra (L2). 1.5 B-cun lateral to the posterior median line.
BL25 (Dachangshu)	In the lumbar region, at the same level as the inferior border of the spinous process of the fourth lumbar vertebra (L4). 1.5 B-cun lateral to the posterior median line.
BL40 (Weizhong)	On the posterior aspect of the knee, at the midpoint of the popliteal crease.
SP6 (Sanyinjiao)	On the tibial aspect of the leg, posterior to the medial border of the tibia, 3 B-cun superior to the prominence of the medial malleolus.
KI3 (Taixi)	On the posteromedial aspect of the ankle, in the depression between the prominence of the medial malleolus and the calcaneal tendon.

*BL* bladder, *SP* spleen, *KI* kidney

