### Interventions

Participants of the LF, HF, and AF groups will be submitted to the treatment protocol, which will consist of the bilateral application of electroacupuncture using a previously calibrated electrostimulator (Sikuro DS100C), consisted of alternating symmetrical biphasic waves with continuous pulse train for the low (2 Hz) or high (100 Hz) frequency groups, and a mixed pulse train for the alternating frequency group (100 Hz and 2 Hz for 3 s each); 100 ms pulse duration and 0.5 ms pulse width; and the maximum current (amplitude) intensity tolerated by the patient and intensified so that sensory habituation is avoided. Trichotomy will be carried out when necessary and the skin will be disinfected with 70% alcohol. With the participant lying down in a ventral position, the needles will be inserted at a 90° inclination with the skin, to a depth at which that the patient reports the “deQi” sensation (≅ 1.5 cm). The protocol sessions will happen twice a week (30 min per session) for five weeks, at no cost to the participants.

Sterile and disposable 0.25 × 30 mm stainless-steel needles (Dong Bang Acupuncture Inc., Seoul, Republic of Korea) will be used. The sessions will last 30 min, twice a week, for five weeks, totaling 10 sessions [10, 26].

The individuals that are randomly assigned to the C and P groups will follow exactly the same protocol as the electroacupuncture groups; however, the C group will not undergo electrical stimulation, as the acupuncturist will activate channels that are not connected to the patient. In the P group, an adhesive moxa (Dong Yang®) will be placed on each acupoint and the needle will be inserted over it, so that the participant only feels the needle prick, but without perforation of the skin and the “deQi” sensation. In addition, as in group C, the electrodes will be connected to the needles; however, no electrical current will be applied [28].

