### Adverse events

At each treatment session, the participants will be asked about any unpleasant and unintended signs or symptoms associated with the use of electroacupuncture. A questionnaire will also be used with a record of the duration and intensity of the adverse symptom reported by the patient, which will be scored according to a Likert-type scale of 1–5, with 1 representing the absence of adverse symptoms and 5 severe adverse symptoms. The severe adverse symptoms will exclude the participant from the treatment and the participant will be referred for medical consultation.

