## Results

This trial still has no results, since it is in the recruitment phase.

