### Trial status

This trial number NCT03802045 is currently in the recruitment phase. The date recruitment started was April 2019 and the expected date for recruitment completion is October 2019. (protocol version 2, 29 March 2019).

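### The published exclusion list has no criterion tied to electrical stimulation, so a person of 60 or over with a pacemaker or implanted defibrillator is eligible as written

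*Protocol article*

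**What the plan says.** Under Recruitment, the article says that "those interested in participating will be selected according to the inclusion and exclusion criteria". The Inclusion criteria section sets the age at 60 or over and asks for chronic non-specific low back pain, a pain score of at least 4, independent walking and consent. The Exclusion criteria section numbers five items: spinal surgery, serious spinal pathology, and then "3) fear of needles; (4) have participated in acupuncture treatment in the previous 30 days; or (5) if they are wheelchair users". It contains no investigator-judgement clause and no general clause on contraindications to the intervention.

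The Interventions section gives current to the low, high and alternating frequency arms, at "the maximum current (amplitude) intensity tolerated by the patient and intensified so that sensory habituation is avoided". The control and placebo arms receive none. Under Procedures, "the acupoints selected for this study will be: BL23, BL25, BL40, SP6, and KI3", which are lumbar and leg points.

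Two other sections bear on safety. Qualification of practitioners asks for specialists with at least three years of experience who are trained in the treatments, "including details such as acupuncture points and manipulation of electroacupuncture parameters". Adverse events has participants questioned at each session and states: "The severe adverse symptoms will exclude the participant from the treatment and the participant will be referred for medical consultation".

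**The concern.** Two of the five exclusions deal with needling: fear of needles and recent acupuncture. None deals with the current, which is the component the trial sets out to compare. The only limit on intensity is what the participant can tolerate. Tolerance reflects sensation and tells the acupuncturist nothing about an implanted device.

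What is at stake is the safety of device carriers in a population recruited at 60 or over. That implanted cardiac electronics call for caution with electrical stimulation is general clinical knowledge; the article does not say so.

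There is also a procedural side. Under Randomization procedures, the acupuncturist opens the envelope immediately before the first session. If a device first came to light then, it would be dealt with after allocation is known and would matter in only three of the five arms. A criterion applied before randomisation avoids that.

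**Working it through.** The finding rests on the text. The arithmetic only sizes the exposure and the cost of the remedy.

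**Step 1: each criterion against the current.**

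| Source | Criterion | Screens for an implanted cardiac device? |
|---|---|---|
| Inclusion | Age 60 or over | No |
| Inclusion | Non-specific low back pain for more than 3 months, with or without leg pain | No |
| Inclusion | Pain score of at least 4 | No |
| Inclusion | Walks independently | No |
| Inclusion | Signed consent | No |
| Exclusion 1 | Previous spinal surgery | No; could catch some devices placed by spinal surgery |
| Exclusion 2 | Serious spinal pathology | No |
| Exclusion 3 | Fear of needles | No |
| Exclusion 4 | Acupuncture in the previous 30 days | No |
| Exclusion 5 | Wheelchair use | No |

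A pacemaker or defibrillator carrier who meets the inclusion criteria passes every row.

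**Step 2: the other safeguards.** The training described names points and stimulation parameters as examples and mentions no device check. The adverse-event rule acts only after symptoms have appeared. Neither screens before randomisation.

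**Step 3: planned exposure** (Sample size and Interventions sections: 25 per arm, five arms, three with current, 10 sessions each).
- Participants assigned current: 3 × 25 = 75, and 75 / 125 = 60%.
- Planned stimulation sessions: 75 × 10 = 750.

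**Step 4: cost of an added exclusion.** The article gives no device prevalence, so p is an assumption, shown over a range. Extra screen failures to reach 125 = 125 / (1 − p) − 125. If carriers were enrolled at the same rate, the expected number assigned current = 75 × p.

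| Assumed p | Extra screen failures | Expected carriers assigned current |
|---|---|---|
| 0.5% | 125 / 0.995 − 125 = 0.63 | 75 × 0.005 = 0.4 |
| 1% | 125 / 0.99 − 125 = 1.26 | 75 × 0.01 = 0.75 |
| 3% | 125 / 0.97 − 125 = 3.87 | 75 × 0.03 = 2.25 |

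The last column counts exposure and says nothing about harm.

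**Step 5: effect on the plan's figures.** The criterion would apply before randomisation and equally to all arms. The target of 125, the planned power and the significance level stay as they are.

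**The case against.** The strongest objection is that this is an omission in a condensed article. Protocol version 2, the SPIRIT checklist, the screening form and the consent form are not shown, and any of them might contain a device exclusion. That stands as a limit: the finding concerns the list as published. It does not remove the point, because a protocol article normally gives its eligibility list in full. This one is numbered to its end and refers the reader nowhere else. If the full protocol already has the exclusion, the sponsor need only confirm it.

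A second objection is that the fault depends on knowledge from outside the article. Who is eligible follows from the article alone. The need for caution is general clinical knowledge and not a figure recalled from a particular source.

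Third, experienced acupuncturists might ask about devices anyway, the training topics are given only as examples, and none of the acupoints is on the chest. These facts lessen the concern for a cardiac device, but they are not a check before randomisation.

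A reader might infer more than the article supports:
- **That participants will be harmed.** The article gives neither a device prevalence nor a risk per exposure.
- **That no implanted device of any kind is covered.** Exclusion 1 could catch some devices placed by spinal surgery, such as some spinal cord stimulators. It does not reach pacemakers or defibrillators.
- **That every contraindication in the stimulator's labelling should be excluded.** The labelling is not shown, so neither the content nor the cost of such a clause can be judged.
- **That the treatment effect would be diluted by a calculable amount.** The Sample size section does not say which arms its 2-point difference separates, so no dilution figure can be derived.

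**Conclusion.** The point holds as a cheap safety improvement. As published, the eligibility criteria admit a person of 60 or over with a pacemaker or implanted defibrillator, and 75 of 125 participants are assigned current at maximum tolerated intensity. The size of any harm cannot be taken from the article, and there is no material effect on the estimates.

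The conclusion assumes that the published list is the list in use, and that caution with implanted cardiac electronics is warranted as a matter of ordinary clinical practice. The screen-failure figures rest on an assumed device prevalence of 0.5% to 3%.

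**What to change.** Add a sixth exclusion: *cardiac pacemaker, implanted defibrillator or other active implanted electronic device*. Check it with one question at screening, before randomisation and before the envelope is opened, and apply it to all five arms so that they stay comparable.

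For enrolled participants still due treatment, ask the same question, give no current to carriers, and keep them in the intention-to-treat analysis. How many this concerns is unclear. The Trial status section says "The date recruitment started was April 2019 and the expected date for recruitment completion is October 2019", whereas the Results section of the article published on 23 December 2019 says "This trial still has no results, since it is in the recruitment phase".

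The cost is a short amendment, one screening question and, at the assumed prevalences, about 1 to 4 extra screen failures. If the full protocol already contains the exclusion, a statement to that effect is enough.

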### Study standard

The study protocol is based on standards established under the Standards for Reporting Interventions in Clinical Trials of Acupuncture (STRICTA) and the Initiative on Methods, Measurement, and Pain Assessment in Clinical Trials (IMMPACT) [12].

### Randomization procedures

The treatment allocation of each eligible individual in the study will be determined by a randomization process. The random allocation to the five arms of the study will be achieved using an online random-number generator (randomization.com) following a balanced 1:1 pattern with a block size of 5. This randomization process will be conducted by an independent staff person who is not involved in the study to guarantee concealment of the allocations. The information on the allocation list will remain strictly confidential. The allocations will be concealed and sequentially numbered; opaque, sealed envelopes will be used to contain the randomization assignments. The acupuncturist will open the envelopes according to the numerical sequence, immediately before the first session of treatment (Fig. 2).

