### Blinding

Patients will remain blinded regarding the category of their allocation throughout the study data collection period. Additionally, the evaluators responsible for the data collection and the outcomes assessor will also be blinded to the patient allocation. The acupuncturist responsible for the interventions will be the only person not blind to the type of treatment to be performed.

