### Sample size

Based on a previous study [11], the sample size was calculated to detect a difference of 2 points on the pain intensity measured by the 11-point pain NRS. In our study, the sample size was calculated using the program G*Power 3 3.1. 9.2, with an estimated standard deviation of 1.47 points [30], a moderate effect size (0.35) [31], a statistical power of 80% (1 β error probability), and an α error level probability of 0.05. The study will require 105 individuals. However, an extra 20% of participants will be added in order to increase the power. Thus, this study will therefore require a total of 125 participants, with 25 in each group.

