### Ethics and data security

All the patients will participate voluntarily and will sign a consent form before randomization. The access and storage of the data will be in accordance with the guidelines of the National Research Ethics Commission (CONEP). This study has been approved by the Ethics Committee of the University of São Paulo Medical School (authorization No. 2.903.991) and in ClinicalTrials.gov under number NCT03802045.

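### A single block size of 5 for five arms makes part of the allocation sequence predictable to the unblinded acupuncturist who opens the envelopes

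*Protocol article*

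**What the plan says.** Under Randomization procedures, the protocol article generates the list online "following a balanced 1:1 pattern with a block size of 5". Procedures describes "five treatment groups, each containing 25 participants", and Sample size gives "a total of 125 participants, with 25 in each group".

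The list and envelopes are protected in three ways:
- List generation: "This randomization process will be conducted by an independent staff person who is not involved in the study", and the list is kept confidential.
- Envelopes: they are sequentially numbered, and "opaque, sealed envelopes will be used to contain the randomization assignments".
- Consent: under Ethics and data security, patients "will sign a consent form before randomization".

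On opening, Randomization procedures says: "The acupuncturist will open the envelopes according to the numerical sequence, immediately before the first session of treatment". Blinding adds: "The acupuncturist responsible for the interventions will be the only person not blind to the type of treatment to be performed". Qualification of practitioners speaks of specialists in the plural and says that they are trained in the protocol. The other sections cited here use the singular.

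The article mentions no second block size. It does not say who screens, enrols or books participants.

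**The concern.** With as many places in a block as there are arms, the remaining arms of a block can be deduced from those already used. Opaque envelopes, a confidential list and prior consent protect an envelope that has not been opened. They do not stop someone who has seen four openings from knowing the fifth. Here the person who sees the openings is the one unblinded member of the team.

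The envelope is opened immediately before the first session, so an envelope is matched to a person by the order in which people start treatment. If that order can be influenced by someone who can predict the next arm, the arms may differ systematically at baseline. Intention-to-treat analysis would not correct this, because the selection would occur before allocation. The planned covariates (age, gender, body mass index and RMQ score) would correct it only in part. One of the primary measures, the NRS, is self-reported, and there are only 25 people per arm.

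**Working it through.** **Inputs.** Five arms in equal ratio and a block size of 5 (Randomization procedures); 125 participants, 25 per arm (Procedures, Sample size).

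**The plan's own figure.** 125 / 5 = 25 complete blocks. Each contributes one person per arm, so there are 25 per arm, as stated.

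**Assumption for the next three steps.** One practitioner sees every earlier opening and knows, or has inferred, the block size.

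**Naming the exact arm.** At position i of a block, 6 − i arms remain and are equally likely, so P(correct) = 1/(6 − i).

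| Position | 1 | 2 | 3 | 4 | 5 |
|---|---|---|---|---|---|
| P(correct) | 20% | 25% | 33% | 50% | 100% |

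The sum is 2.283 correct calls per block, a mean of 2.283 / 5 = 45.7%, or about 57 of 125. Chance is 20%. Only position 5 is certain: 25 of 125 (20%).

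**Electroacupuncture (3 arms) versus not (2 arms).** The call is certain when all remaining arms are of one kind.
- Position 5: always, 1.
- Position 4: the two remaining arms are of one kind, (3 + 1)/10 = 0.4.
- Position 3: the three remaining arms are all electroacupuncture, 1/10 = 0.1.
- Positions 1 and 2: never.

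The total is 1.5 / 5 = 30%.

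**Placebo versus not.** The call is certain once placebo has been used, or at position 5: (0 + 0.2 + 0.4 + 0.6 + 1)/5 = 44%, or 55 of 125.

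**If openings are not shared.** Assume, for illustration, two practitioners, patients split at random and no exchange of information. Each earlier opening in the block is then seen with probability 1/2. The mean of correct calls is (0.200 + 0.225 + 0.258 + 0.306 + 0.388)/5 = 27.5%. Certainty at position 5 needs all four earlier openings to have been seen: 20% × 1/16 = 1.25%.

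**Varying blocks of 5, 10 and 15, equally likely (an assumption).**
- *Each block's size known.* The expected number of certain calls per block is 1 for size 5, 1 + 1/9 = 1.111 for size 10, and 1 + 2/14 + (2/14)(1/13) = 1.154 for size 15. The share is (1 + 1.111 + 1.154)/30 = 10.9%. By simulation, best guesses are right 40.1% of the time, and electroacupuncture versus not is certain for about 17%.
- *Only the set of sizes known.* Simulation of sequences of 125 with an optimal guesser gives certain calls for about 3% and correct guesses for about 40%.

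Varying the blocks therefore removes most of the certainty if sizes stay hidden. It removes only 45.7 − 40.1 = 5.6 of the 45.7 − 20 = 25.7 percentage points of excess guessing accuracy.

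**The case against.** The strongest reply is that predicting an allocation harms nothing unless the prediction can be acted on. The article randomises people who are already eligible and have consented, baseline assessment comes before treatment, and the evaluators are blinded. Nowhere is the acupuncturist said to screen, enrol, book or defer anyone. This stands as a limit. Who books first sessions is a detail that an article commonly leaves to the full protocol, so its absence is not criticised here. What remains is a stated rule that makes part of the sequence predictable. A different rule would avoid much of the certainty at almost no cost.

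The reply also holds that one all-seeing practitioner is an assumption. That is right: the plural under Qualification of practitioners allows several, and the two-practitioner illustration shows how far the figures then fall. If practitioners compare notes, the full figures return.

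A reader might infer that printing the block size in a journal exposed the sequence. The dates do not support this. The article appeared on 23 December 2019, and recruitment was expected to end in October 2019. Training in the protocol could reveal the block size, and a pattern of one of each arm is easy to notice, so publication is not needed for the point.

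**Conclusion.** The point holds as a modest design weakness that is cheap to improve. A fixed block equal to the number of arms, opened in sequence by the unblinded practitioner, weakens concealment. At most, 20% of exact allocations and 30% of electroacupuncture-versus-not allocations are certain, with 46% of best guesses correct against 20% by chance.

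These maxima assume that one person sees every opening and recognises the block pattern. Bias further requires that this person can affect the order in which people start treatment.

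A reader might go further and infer that concealment is absent, or that allocation was in fact manipulated. The documents support neither. The list, the envelopes and consent before randomisation are real safeguards, and no control over booking is described.

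**What to change.** For participants not yet randomised:

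1. Once the current block of five is complete, have the independent staff member regenerate the remaining list with randomly varying block sizes, for example 5, 10 and 15. Do not disclose the sizes to the practitioners.
2. Assign envelope numbers by a participant number that the blinded evaluator fixes at baseline, before the acupuncturist is involved. The order of first sessions then no longer decides who receives which envelope. This step matters more than the first, because guessing accuracy stays near 40% even with varying blocks.

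The cost is one new list and one line in the baseline procedure. The downside is a possible small imbalance. If a block of 10 or 15 is unfinished at 125, it holds 5 or 10 people, with 1 or 2 expected per arm. In a block of 15 an arm's count can range from 0 to 3, so with 5 people the largest deviation is 3 − 1 = 2, and with 10 people it is 2 − 0 = 2. In a block of 10 it is at most 1. No arm can therefore differ from 25 by more than 2. Choosing block sizes that sum to the number remaining avoids any imbalance.

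Trial status still describes recruitment as under way, but on the stated timetable few or no participants may remain. If recruitment is complete, report the fixed block size, who saw the openings and the resulting predictability as a limitation.
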